**REVISION HISTORY**

| Version | Date | Amendment Text | Description |
| --- | --- | --- | --- |
| 1.1 | 2020/03/06 | Adjustment of description |  |
| 1.2 | 2020/03/10 | Adjustment of description |  |
| 1.3 | 2020/03/25 | Adjustment of description |  |
| 2.0 | 2020/07/01 | Consent withdrawal document addition  Co-Investigators addition  Adjustment of description |  |
| 2.1 | 2020/09/01 | Co-Investigators addition  Adjustment of description |  |
| 2.2 | 2021/01/27 | Extension of research period  Co-Investigators addition  Adjustment of description |  |
| 2.3 | 2021/04/20 | Extension of research period  Co-Investigators addition |  |
| 2.4 | 2021/07/21 | Co-Investigators addition  Adjustment of description |  |
| 2.5 | 2021/09/10 | Co-Investigators addition  Adjustment of description |  |
| 2.6 | 2022/02/07 | Adjustment of description |  |

# 1. TRIAL SUMMARY

World Health Organization Registration Data Set

| Title | Prevalence of psychological distress, quality of life, and satisfaction among patients and family members following comprehensive genomic profiling testing: Protocol of the Quality of Life for Cancer genomics and Advanced Therapeutics (Q-CAT) Study |
| --- | --- |
| Primary registry and trial identifying number | Japan Registry of Clinical Trials: RCT1030200039 |
| Sources of monetary or material support | This work is supported by Japan Society for the Promotion of Science (JSPS) grant number 20K21742 and Daiwa Securities Health Foundation. |
| Central contact | [name], PhD  National Cancer Center Hospital  [name]  [contact] [name] |
| Study officials/Investigators | [name]  National Cancer Center Hospital  [name]  [contact], [name]  [contact]  Study Principal Investigator |
| Brief title | Protocol of the Quality of Life for Cancer genomics and Advanced Therapeutics (Q-CAT) Study |
| Acronym | Q-CAT |
| Countries of recruitment | Japan |
| Interventions | None |
| Key eligibility criteria | Age eligibility: No limit  Sex eligibility: Both  Accepts healthy volunteers: No  Inclusion criteria:  1. Patients at National Cancer Center Hospital  2. Patients pathologically diagnosed as malignant solid tumor  3. Patients planned to perform comprehensive cancer genome profiling  4. Patients with written informed consent  5. Family member of patients consented to this trial  6. Family member of patients who also attend the appointment for result of comprehensive cancer genome profiling  7. Family member of patients with written informed consent  Exclusion criteria:  1. Patients with difficulty writing and reading Japanese  2. Patients who was others judged by the investigator to be unsuitable for the study  3. Family member of patients with difficulty writing and reading Japanese  4. Family member of patients who was others judged by the investigator to be unsuitable for the study |
| Study design | Primary purpose: Supportive Care  Phase: Observational study |
| Date of first enrollment | May 18, 2020 |
| Target sample size | 500 |
| Recruitment status | Ongoing |
| Primary outcomes | Outcome: Prevalence of depression  Timeframe: at before comprehensive cancer genome profiling test, at the time of explanation of the result, at three times after the test, at the six months after the test |
| Secondary outcomes | Outcome: Anxiety, QOL, Symptom, Satisfaction, Quality of communication, Knowledge of comprehensive cancer genome profiling test, social support, Medical background, Social background, Medical information  Timeframe: at before comprehensive cancer genome profiling test, at the time of explanation of the result, at three times after the test, at the six months after the test |

# 2. INTRODUCTION

## 2.1. Background and rationale

On May 29th 2019, two cancer genomic profiling, CGP tests were reimbursed in Japan; which were "Onco GuideTM NCC Oncopanel system" and "Foundation One CDx". Recently the testing can be only allowed once in a lifetime for those who are advanced cancer patients with no standard therapy, or those who are advanced cancer patients finished standard therapies. The cost of the testing is very expensive that costs total ¥560,000 JPY, however the potential benefit patients enjoy from the cancer genomic profiling testing is individualized genomically appropriate therapeutics, on a word making precision oncology reality. In some malignancy, they already have companion diagnostic tools to survey one or two specific gene that allows to use genetically target therapy which has higher response rate and long survival benefit, such as EGFR-TKIs in non-small cell carcinoma (Maemondo et al., 2010, Mitsudomi et al., 2010). Even in these cancers with companion diagnostic tools, cancer genomic profiling testing sometimes allows to find rare but very effective actionable gene. Interestingly, about 10-20% of those who underwent testing CGP testing finally led to genetically matched therapies (Sunami et al., 2019). As these statistics shows that the ratio who receive benefit from CGP testing is not so much, the growing expectation and focus is not matching its clinical benefit ratio result in disappointment and mental burden both in cancer patients and their family members. There is research of CGP influence on mental health on breast hereditary cancer from Spain and on breast and cervical hereditary cancer from United States; we Japanese don't have any data on mental influence of CGP testing. Spanish research is multi-centered of 30cites with 187 candidates recruited with 4 times of follow up survey asking anxiety, mental burden (Esteban et al., 2018). Research from United States enrolled 232 patients and surveyed psychological impact, understanding (Lumish et al., 2017). Both of the research is focused on only hereditary cancers using germ cell cancer panels and suggest some negative impact toward mental health. They did not show the prevalence rate, clinical course, relative factors nor impact toward family members. Our research focus on not only germ cell mutation but also somatic mutation in CGPs. Moreover, 167 hospitals are selected to perform CGP in Japan, taking account of more limited hospital running clinical trials, there is surely difficulties to access the cites of clinical trials if patients luckily found to have rare actionable genomic alteration. According to Townsley & Selby（2005）'s report that reviewed the preventing factors of cancer patients who had difficulties to be enrolled to clinical trial, revealed that lack of social support had highly impacted against enrollment  It goes without saying that social support will be essential issue for patients with rare actionable mutation to be enrolled to genetically matched clinical trial. To make long story short, our study focusing to reveal the reality of patients and family members who underwent CGP testing toward longitudinal mental and psychological impact, social support, and QOL is essential for accurate and precise understanding of cancer patients with CGP testing.

## 2.2. Objectives

The aims of this study are to identify the prevalence of psychological distress, quality of life, and satisfaction with CGP testing among patients and their family members by gathering electronic patient-reported outcomes and qualitative data.

## 2.3. Trial design

This is an observational study. Participants are asked to undergo questionnaire, otherwise there is no intervention takes place.

# 3. METHODS

## 3.1. Study setting

This is a single institute observational study done in National Cancer Center Hospital   Japan.

## 3.2. Eligibility criteria

### 3.2.1. Inclusion criteria

1. Patients at National Cancer Center Hospital
2. Patients pathologically diagnosed as malignant solid tumor
3. Patients planned to perform comprehensive cancer genome profiling
4. Patients with written informed consent
5. Family member of patients consented to this trial
6. Family member of patients who also attend the appointment for result of comprehensive cancer genome profiling
7. Family member of patients with written informed consent

### 3.2.2. Exclusion criteria

1. Patients with difficulty writing and reading Japanese
2. Patients who were others judged by the investigator to be unsuitable for the study
3. Family member of patients with difficulty writing and reading Japanese
4. Family member of patients who was others judged by the investigator to be unsuitable for the study

## 3.3. Interventions

This is an observational study. Participants are asked to undergo questionnaire, otherwise there is no intervention takes place.

## 3.4. Outcomes

Primary outcome:

Depression

The nine items of Patient Health Questionnaire-9 (PHQ-9) [Spitzer et al., 1999] will be used to measure depression. Higher scores indicate greater possibility of major depression (a PHQ-9 score ≥10, the cut off score, had a sensitivity of 88% and a specificity of 88% for major depression).

Secondary outcomes:

Anxiety

The seven items of General Anxiety Disorder-7 (GAD-7) [Spitzer et al., 2006] will be used to measure anxiety. Higher scores indicate greater possibility of generalized anxiety disorder (a GAD-7 score ≥10 had a sensitivity of 89% and specificity of 82% for generalized anxiety disorder).

QOL

The 30 items of the European Organization for Research and Treatment of Cancer Quality of Life Questionnaire module Core 30 (EORTC QLQ−C30) [Aaronson et al., 1993] will be used to measure QOL. For global QOL scale and functional scales, higher score indicates a better level of function. For symptom-oriented scales, higher scores indicate more severe symptoms.

Symptoms

The nine items of the Edmonton Symptom Assessment System (ESAS) [Yokomichi et al., 2015] will be used to measure symptoms. High scores indicate greater morbidity.

Qualitative interviews

All participants with a PHQ-9 score above cut-off, and a small convenience-selected subset of participants will be invited at baseline and at each follow-up time-point to participate in structured interviews based on SCID-IV [JAMA, 2015].

Knowledge

A 10-item, multiple choice, study-developed questionnaire will be used to assess knowledge of the purpose of CGP testing, likely frequency of informative results, cancers in which informative results are more likely to be found, availability of tailored treatment options, and source of genetic knowledge. Scores will be summed from 0 to 10, with high scores indicating greater knowledge.

Satisfaction

The five items of the Patient Satisfaction Questionnaire (PSQ) will be used to measure satisfaction. Lower scores indicate higher satisfaction. [Blanchard et al., 1986]

Quality of communication

The 11 items on the quality of communication in the Health Information National Trends Survey (HINTS) will be used to measure quality of communication. High scores indicate greater communication.  [Smith et al., 2015]

Social support

## 3.5. Participant timeline

[figure not shown]

## 3.6. Sample size

The Q-CAT study plans to recruit 300 patients and 200 family members over a one-year period. These sample sizes were estimated based on the fact that an average of 33 patients were tested from September to October 2019, suggesting that 396 patients will be tested over a one-year period in our institute. Given an estimated participation rate in our QCAT trial of 75%, we determined a sample size of 300. For family members, an estimated sample size of 192 was chosen, based on an accompaniment rate by family members of patients visiting our outpatient clinic of 80%, with a consent rate of 80%.

## 3.7. Data collection

### 3.7.1. Trial procedures and evaluations

The Q-CAT (QOL for Cancer Genomics and Advanced Therapeutics among Patients and Their Family Members) study is being conducted as a psycho-social/ethical study with long span of four times; at the time of consent of CGP testing (T0), at receipt of the result of CGP testing (T1), three months after receipt of the result of CGP testing (T2), six months after receipt of the result of CGP testing (T3). By following candidate for enough duration of time, we could evaluate both immediate and gradual reality in psychosocial influence of CGP testing toward patients and their family members.

### 3.7.2. Retention

**Participant Withdrawal**

Participants, both patients and family members, may withdraw from the study for any reason at any time. The investigator also may withdraw participants from the study in order to protect their safety and/or if they are unwilling or unable to comply with required study procedures after consultation with protocol Chair.

## 3.8. Data management

Participants will be asked to complete a questionnaire using an electronic patient reported outcome (ePRO) application software or hard copy at baseline (T0), 1 to 4 weeks after receiving the results of CGP testing (T1; approximately 2–3 months post baseline), 3 months (T2) after T1, and 6 months (T3) after T1. These timeframes have been chosen to allow the impact of the test results to be captured in both the short term (when a treatment decision is being made) and longer term (while undergoing or close to completion of the targeted therapy, if adopted). All patients with a PHQ-9 score at the cutoff point of 10 or above (total score) as well as a small subset of participants (around 20–40) selected as a convenience sample who score below this cutoff point will be interviewed using the Structured Clinical Interview for DSM-V-RV (SCID), which includes items on mood disorders, neurotic, stress-related and somatoform disorders, and behavioral syndromes associated with physiological disturbances and physical factors, at each assessment time-point to determine the 4-week and lifetime prevalence rates of comorbid mental disorders

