## 3.9. Statistical methods

### 3.9.1. Outcomes

To examine the possibility of selection bias, a comparative analysis of respondents and non-respondents will be conducted based on demographic and clinical data. Estimates of the prevalence of depression, anxiety, and other mental comorbidity in the target population will be reported as unadjusted raw rates observed in the total sample. Descriptive statistical analysis will be conducted for all data. Temporal changes in scales will be investigated by calculating differences between time-points. Comparisons of demographic and other factors will be conducted using the t-test and ANOVA, and Kruskal-Wallis test. Associations between variables will be examined using correlation analysis, chi-squared tests and regression analysis, depending on the presence or absence of depression and anxiety based on outcome scores. Multiple or logistic regression analysis will be used to adjust for the effects of confounders and to identify predictors of outcome. All analyses will be performed using IBM SPSS Statistics Version 26.

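### The diagnostic interview is meant to give prevalence of non-mood disorders but is triggered only by the depression score, so with raw total-sample rates the interview-based prevalence of anxiety-type disorders is biased downward

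*Protocol*

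**What the plan says.** **Who is interviewed.** Protocol section 3.8 names "All patients with a PHQ-9 score at the cutoff point of 10 or above (total score) as well as a small subset of participants", the subset being "around 20–40) selected as a convenience sample who score below this cutoff point will be interviewed". Section 3.4 gives the same rule: "All participants with a PHQ-9 score above cut-off, and a small convenience-selected subset of participants will be invited at baseline and at each follow-up time-point". No other scale is named as a trigger.

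**What the interview covers.** Section 3.8 describes an instrument "which includes items on mood disorders, neurotic, stress-related and somatoform disorders, and behavioral syndromes associated with physiological disturbances and physical factors". Its stated purpose is "to determine the 4-week and lifetime prevalence rates of comorbid mental disorders".

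**What the scales are supported for.** Section 3.4 gives PHQ-9 of 10 or above a sensitivity and specificity of 88% each, for major depression. For the anxiety scale it states that "a GAD-7 score ≥10 had a sensitivity of 89% and specificity of 82% for generalized anxiety disorder".

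**How prevalence is reported.** Section 3.9.1: "Estimates of the prevalence of depression, anxiety, and other mental comorbidity in the target population will be reported as unadjusted raw rates", with the total sample as denominator.

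**The concern.** A depression screen decides who enters an interview that is also meant to count disorders not led by depression. A participant with GAD-7 of 10 or above and PHQ-9 below 10 is interviewed only if picked by convenience, and that pick takes no account of GAD-7.

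The rate is taken over the total sample without adjustment, so anyone not interviewed enters the denominator and can never enter the numerator. The loss grows with the share of a disorder's cases that score below 10 on PHQ-9. That share is likely to be larger for anxiety-type disorders than for depression, which PHQ-9 was built to detect. At stake are the interview-based prevalence of non-mood disorders and the comparison of disorder groups after genomic testing. A later analysis plan cannot recover interviews that were never held.

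**Working it through.** **The plan's own figures.** The protocol gives no interview-based prevalence to reproduce. Its patient sample size does reproduce: 33 × 12 = 396 per year, and 396 × 0.75 = 297, against 300 stated. For family members, 300 × 0.8 × 0.8 = 192, as stated, with a recruitment target of 200.

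**Inputs from section 3.8 and section 3.6.** N = 300 patients; c = 20 to 40 below-cutoff interviews, taken here as available at each time-point and used for patients.

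**Assumptions, not in the protocol.**
- PHQ-9 positive: 15 to 25% of patients.
- s, the share of anxiety-type cases with PHQ-9 of 10 or above: 0.5 to 0.8.
- True prevalence p = 10%.
- The convenience subset behaves like a random sample.

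**Step 1: coverage of PHQ-9 negatives.** f = c / (N × (1 − PHQ-9-positive share)).
- Lowest: 20 / (300 × 0.85) = 20 / 255 = 0.078.
- Highest: 40 / (300 × 0.75) = 40 / 225 = 0.178.

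**Step 2: recorded prevalence.** Recorded = p × [s + (1 − s) × f].
- s = 0.5, f = 0.078: 10% × (0.5 + 0.5 × 0.078) = 5.4%.
- s = 0.8, f = 0.178: 10% × (0.8 + 0.2 × 0.178) = 8.4%.

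With s = 0.4 the recovered share of cases falls to 45 to 51%.

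**Step 3: the same formula for major depression.** Here s can be taken from section 3.4, at 0.88.
- f = 0.078: 10% × (0.88 + 0.12 × 0.078) = 8.9%.
- f = 0.178: 10% × (0.88 + 0.12 × 0.178) = 9.0%.

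Mood diagnoses are also undercounted, but by less than anxiety-type diagnoses whenever s for the latter is below 0.88.

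**Step 4: how many are GAD-7 positive only.** I used a bivariate normal model with PHQ-9 positive 15 to 25%, GAD-7 positive 10 to 20% and latent correlation 0.6 to 0.8, all assumed. At 20% and 15% positive with correlation 0.7, the GAD-7-only share is 5.7%, or 300 × 0.057 = 17 patients. Over all combinations the count is about 4 to 36 of 300.

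The accuracy figures in section 3.4 point to more GAD-7 positives than that. At 10% generalized anxiety disorder, 0.89 × 0.10 + 0.18 × 0.90 = 25.1% would screen positive. At 25% GAD-7 positive the same model gives 24 to 47 of 300. Of those positives, 0.162 / 0.251 = 65% would be false, so GAD-7-only positives are not a count of missed disorders.

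**The case against.** **Anxiety prevalence is already measured by GAD-7.** This stands. The questionnaire goes to all participants, and section 3.9.1 classifies anxiety by outcome scores. A reader might infer that all reported anxiety prevalence is too low, and the protocol does not support that. Only interview-based diagnoses are affected. They still matter: section 3.8 gives the interview its own prevalence aim, and the other mental comorbidity named in section 3.9.1 has no source but the interview.

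**The undercount comes from sampling and weighting, not from the choice of screener.** Largely true. A PHQ-9 gate would give unbiased prevalence for any disorder if the negatives were sampled at a known fraction and weighted. The screener's own contribution is the larger loss for disorders not led by depression, and poor efficiency: few anxiety-type cases would turn up among 20 to 40 unselected PHQ-9 negatives. The remedy therefore has to deal with both.

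**The direction depends on the denominator.** True. Over interviewed participants only, the rate would usually be too high: a true 15% with s = 0.6 would show as 26 to 44%. Section 3.9.1 names the total sample, so downward is the direction under the plan as written.

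**The interview is a minor component.** Depression is the primary outcome, section 3.4 lists the interview under a qualitative heading, and comorbid could mean accompanying depression. On that last reading a PHQ-9 gate would be natural. The reference to the target population in section 3.9.1 tells against it without excluding it. This limits the weight of the point but does not remove it.

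**GAD-7 does not screen for everything listed.** Correct. The protocol supports it for generalized anxiety disorder only, so adding it would not by itself capture stress-related or somatoform disorders.

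**Conclusion.** The point holds for interview-based prevalence of non-mood disorders, and only there. Followed exactly, the plan records too low a rate for anxiety-type diagnoses, probably with a larger shortfall than for mood disorders.

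The direction follows from the protocol's own trigger and denominator, provided some cases score below 10 on PHQ-9. The size does not: 5.4 to 8.4% recorded for a true 10% assumes that 20 to 50% of cases score below the cutoff, that 15 to 25% of patients are PHQ-9 positive, and that the convenience interviews act as a random sample.

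A reader might also infer that the GAD-7-only participants would fit comfortably into the 20 to 40 places. The figures do not show that. The count ranges from about 4 to 47 of 300 patients depending on the assumptions, before any of the 200 family members. Whether family members are interviewed at all is unclear, since section 3.4 speaks of participants and section 3.8 of patients.

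This should be corrected, but it does not touch the primary outcome.

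**What to change.** In sections 3.4 and 3.8, keep the PHQ-9 trigger and divide the planned 20 to 40 below-cutoff interviews into two strata, using the GAD-7 score already collected:

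1. GAD-7 of 10 or above with PHQ-9 below 10, oversampled.
2. Both scores below 10, with a reserved share of places.

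Select at random within each stratum at a recorded fraction. In section 3.9.1, replace the raw rate for interview-based diagnoses with (PHQ-9-positive cases + stratum 1 cases / f1 + stratum 2 cases / f2) / N. State whether the 20 to 40 applies per time-point and whether it includes family members.

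**Cost.** Wording in three sections and one flag in the questionnaire report; no new data and no more planned interviews. The price is fewer double negatives, hence larger weights. As an illustration, take 60 PHQ-9 positives, 17 GAD-7-only and 300 − 60 − 17 = 223 double negatives, with 30 places split 15 and 15. Each case found in stratum 2 then carries a weight of 223 / 15 = 14.9 and adds 14.9 / 300 = 5.0 percentage points. If the 30 were drawn at random from all 240 PHQ-9 negatives, the weight would be 8 and each case would add 2.7 points. Stress-related and somatoform disorders would still rest largely on stratum 2, so their estimates will be imprecise and need intervals. Not every GAD-7-only participant may get a place.

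**If the PHQ-9-only trigger and raw rates stay:** report no total-sample interview-based prevalence for non-mood disorders, and describe those diagnoses only as comorbidity among PHQ-9-positive participants. This costs nothing beyond the narrower claim.

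### The SCID-based prevalence of mental disorders will be too low, because few screen negatives are interviewed and the plan reports raw rates in the total sample

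*Protocol*

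**What the plan says.** Protocol section 3.8 sets a two-step scheme at each assessment time-point. Patients at or above the PHQ-9 cutoff of 10 are all interviewed. Below the cutoff, "a small subset of participants (around 20–40) selected as a convenience sample who score below this cutoff point will be interviewed". The stated purpose is "to determine the 4-week and lifetime prevalence rates of comorbid mental disorders", and the interview covers mood, neurotic, stress-related and somatoform disorders among others.

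Section 3.4 describes the same scheme under its heading on qualitative interviews: "All participants with a PHQ-9 score above cut-off, and a small convenience-selected subset of participants will be invited at baseline". The invitation is repeated at every later time-point. Section 3.4 also states that a PHQ-9 score of at least 10 "had a sensitivity of 88% and a specificity of 88% for major depression".

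Section 3.9.1 fixes the estimator. Its subject is "Estimates of the prevalence of depression, anxiety, and other mental comorbidity in the target population". The rule it sets for these is that they "will be reported as unadjusted raw rates observed in the total sample". No weighting is described, and sections 3.9.2 and 3.9.3 read N/A.

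**The concern.** Whether a person is interviewed depends on the screen result. Above the cutoff nearly everyone is to be interviewed; below it, only a small minority. A raw rate over the total sample has no diagnosis for the un-interviewed negatives and so treats them as non-cases.

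The raw-rate rule reaches the SCID results. PHQ-9 supplies depression and GAD-7 supplies anxiety, and the SCID is the only listed instrument that can supply other mental comorbidity. The published diagnostic prevalence would therefore depend partly on how many negatives happened to be interviewed. The error grows for conditions that PHQ-9 does not target, and for lifetime diagnoses, where someone with a past disorder need not score 10 or more now.

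Convenience selection adds a second problem. The chance of being interviewed is unknown, so the results cannot be weighted back to the whole sample with any assurance.

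**Working it through.** **Inputs.** From section 3.6: N = 300 patients. The feasibility arithmetic behind this is 33 × 12 = 396 and 396 × 0.75 = 297, rounded to 300. From section 3.4: Se = Sp = 0.88, for major depression. From section 3.8: m = 20 to 40 negatives interviewed. The protocol gives no expected prevalence, so p is assumed over 5–30%, with 15% worked in full. The SCID is taken as the truth, all positives are taken as interviewed, and 20–40 is read as the number per time-point.

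**Screen result at p = 15%.**
- True positives: 300 × 0.15 × 0.88 = 39.6
- False positives: 300 × 0.85 × 0.12 = 30.6
- False negatives: 300 × 0.15 × 0.12 = 5.4
- True negatives: 300 × 0.85 × 0.88 = 224.4
- So 70.2 positives and 229.8 negatives. The disorder rate among negatives is 5.4 / 229.8 = 2.35%.
- Negatives never interviewed: 1 − 40/229.8 = 83% to 1 − 20/229.8 = 91%.

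**Rate as the plan defines it (total sample).** Cases found = 39.6 + m × 0.0235.
- m = 20: 40.07 / 300 = 13.4%
- m = 40: 40.54 / 300 = 13.5%

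The relative shortfall is (1 − Se) × (1 − m/negatives). This is 0.12 × 0.913 = 11.0% for m = 20 and 0.12 × 0.826 = 9.9% for m = 40. Over p = 5–30% it stays at about 10–11%.

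**Disorders that PHQ-9 detects less well (assumed accuracy).**
- Se 0.60, Sp 0.85: about 0.40 × (0.81 to 0.92), a shortfall of 33–37% over p = 5–30%.
- Se 0.50, Sp 0.88, p = 15%, m = 30: negatives = 22.5 + 224.4 = 246.9, and the shortfall is 0.50 × (1 − 30/246.9) = 44%, that is 8.4% against 15%.

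**Dividing by those interviewed instead (p = 15%, 88%/88%).** 40.07 / 90.2 = 44.4% for m = 20 and 40.54 / 110.2 = 36.8% for m = 40, or 2.5–3.0 times the truth.

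**Two-phase weighted estimate.** Positives get weight 1 and negatives get weight 229.8/m. The expected value is (39.6 + 229.8 × 0.0235) / 300 = 15.0%, provided the negatives are a probability sample. The negatives add a standard error of (229.8/300) × √[0.0235 × 0.9765 / m × (1 − m/229.8)], which is 2.5 points for m = 20 and 1.7 points for m = 40. If a convenience sample carried 0 to 3 times the true rate, the weighted estimate would run from 39.6/300 = 13.2% to (39.6 + 16.2)/300 = 18.6%.

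**Total error at p = 15% (mean squared error, points squared).**
- Major depression, raw: m = 20, 1.64² + 13.36 × 86.64/300 = 6.6; m = 40, 6.1.
- Major depression, weighted: m = 20, 15 × 85/300 + 2.48² = 10.4; m = 40, 7.0.
- At an assumed sensitivity of 50%: raw 42–50, weighted 16–30.

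**The case against.** The best defence is that little of the study is touched. The primary outcome is depression by PHQ-9, anxiety is by GAD-7, and everyone completes both. The SCID is absent from the secondary outcomes listed in the trial summary, and section 3.4 files it under qualitative interviews. For major depression the bias at 15% is about 1.6 points, less than the ordinary sampling error of √(0.15 × 0.85/300) = 2.1 points. All of that stands and limits the point. It does not remove it, because section 3.8 names prevalence as the purpose of the interview.

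The remedy can also be attacked. With 20–40 negatives, only 0.5–0.9 cases are expected among them at 15%, and the chance of finding none is 39–62%. Weighting then buys freedom from bias at the price of variance and does not lower total error for major depression at that prevalence. Splitting so few interviews into several strata would make this worse. This stands too, though weighting does lower total error at 15% if sensitivity is only 50%.

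A reader might infer that all the study's prevalence figures are biased, or that the plan would report something like 40% where the truth is 15%. Neither follows. The questionnaire rates have no verification step, and section 3.9.1 names the total sample as denominator, not those interviewed.

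A separate analysis plan could not settle this as mere detail, since the protocol itself fixes both the convenience selection and the unadjusted rate. The comparison of respondents with non-respondents in section 3.9.1 concerns response, not selection for interview.

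**Conclusion.** The point holds for SCID-based prevalence only. Followed as written, the plan understates it. The relative shortfall is about 10–11% for current major depression, on the protocol's 88%/88%, 300 patients and an assumed prevalence of 5–30%. It is about 33–37% at an assumed sensitivity of 60% and about 44% at 50%; those two sensitivities are illustrations, not figures from the protocol. The direction does not depend on the assumptions so long as some un-interviewed negatives have a disorder.

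Two wording conflicts stand beside this and do not cause the bias. Section 3.4 speaks of participants and section 3.8 of patients, so it is unclear whether screen-positive family members are interviewed. Section 3.4 names SCID-IV and section 3.8 a DSM-V version. A reader might also see a conflict between scoring above the cut-off (3.4) and at or above 10 (3.8). That is loose wording, since section 3.4 itself defines the cut-off as a score of at least 10.

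**What to change.** 1. In section 3.9.1, exempt SCID outcomes from the rule that prevalence is an unadjusted raw rate in the total sample.
2. For interviews already done by convenience, report SCID results descriptively among those interviewed, separately for PHQ-9 of 10 or more and below 10. Limit population prevalence statements to PHQ-9 and GAD-7. Recruitment has been open since May 2020, and a random list cannot repair these interviews afterwards.
3. For remaining interviews, draw the below-cutoff interviewees by a simple random draw, without further strata, and record the sampling fraction at each time-point. Report a two-phase weighted prevalence with design-based confidence intervals.
4. Reconcile sections 3.4 and 3.8 on whether screen-positive family members are interviewed and on the SCID edition, and state whether 20–40 is per time-point or overall.

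The cost is protocol wording and a random list, with no extra interviews. The downside is a wider interval: the negatives add a standard error of about 1.7–2.5 points at 15% prevalence. For major depression at that prevalence the gain is an unbiased estimate, not a smaller total error.
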